### Statistical principles

The primary analysis will be conducted based on the intention-to-treat principle. Specifically, each randomised intubation encounter will be analysed based on the allocated treatment group, independent of compliance with the treatment delivered.

A per-protocol analysis including all intubation attempts where a study therapy was commenced (regardless of whether it was the therapy that was randomised) will also be undertaken and reported in the supplementary material.

The unit of analysis for most outcomes is the intubation encounter. If patients are required to be intubated more than once, they can be re-enrolled and re-randomised, theoretically receiving different study interventions for each intubation attempt within a single admission. For secondary outcomes relating to admission (i.e. ventilator-free days, length of ICU and hospital stay and death), only those patients with one enrolment per admission will be included in the primary and per-protocol analyses.

Statistical tests will be two-sided applying a statistical significance level of 0.05, although the primary outcomes will be analysed at a level of 0.025 (applying Bonferroni’s correction). We will not apply a formal correction for multiple testing to any of the subgroup analyses, sensitivity analyses or to the secondary outcomes. We will ensure conclusions drawn as a result of analyses are interpreted with deference to multiple comparisons.

If there is more than 10% of data missing for the primary outcomes, a sensitivity analysis using multiple imputation will be undertaken.

Continuous variables will be assessed for normality; this will be undertaken using visual inspection of histograms and *Q*-*Q* plots.

Descriptive statistics will be used when summarising variables; frequencies (percentages) for discrete variables, mean and standard deviation (SD) for normally distributed continuous variables, or, if continuous variables are non-normally distributed, median with interquartile range (IQR).

Subgroup analyses will be executed regardless of any potential treatment effect on the primary or secondary outcomes in the main cohort.

Changes to the analysis plan by the investigators effective after the publication of this SAP will be declared as such.

The statistical analysis will be undertaken using StataSE version 17 (StataCorp Pty Ltd., College Station, TX).

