Lowest oxygen saturation in the 2 min immediately following an intubation attemptLowest oxygen saturation throughout total intubation encounter (defined as the first insertion of laryngoscope to successful intubation)Duration of invasive mechanical ventilation, defined as the start of successful intubation to extubationVentilation-free days (VFD), defined as the duration of respiratory support for all episodes with an ETT in situ for the first 28 days after randomisation censored at 28 days; VFD will be recorded as 0 in patients that died within 28 days after randomisationLength of ICU stay measured in days, defined as the start of successful intubation to ICU discharge, and limited to patients with an ICU admissionLength of hospital stay measured in days, defined as the start of successful intubation to hospital dischargeOccurrence of minor tracheal intubation-related adverse events (TIAEs) defined as one of the following in the period starting at the commencement of the intubation attempt until 2 min after successful intubation:Bradycardia, not requiring treatmentHypotension, not requiring treatmentMain stem bronchial intubationOesophageal intubation with immediate recognitionEmesis without aspirationEpistaxisDental or lip traumaOccurrence of major TIAEs defined as one of the following in the period starting at the commencement of the intubation attempt until 2 min after successful intubation:Cardiac arrest with or without return of spontaneous circulationOesophageal intubation with delayed recognition (> 60 s)Emesis with aspirationHypotension requiring treatmentBradycardia requiring treatmentLaryngospasmMalignant hyperthermiaPneumothorax or pneumomediastinumDeath, defined as death during current hospital admission

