#### Adverse events and protocol deviations

All adverse events defined in the study protocol will be reported as described in Table 3 and compared between the two study groups using logistic regression as described above for secondary outcomes (Table 4). Protocol deviations will be tabulated and reported in the supplementary material.

**Table 4 Tab4:** Secondary outcomes in the total trial cohort

Outcome	Standard care, *N* =	THRIVE, *N* =	Estimate of difference (95% CI)^a^	Adjusted estimate of difference (95% CI)^b^
Number of intubation attempts, *median (IQR)*				
Number of intubation attempts with rescue oxygenation, *median (IQR)*				
Lowest oxygen saturation throughout total intubation period, *median (IQR)*				
Duration of mechanical ventilation, *median (IQR)*				
Ventilation free days, *median (IQR)* ^c^				
Length of ICU stay (days), *median (IQR)* ^c,^ ^d^				
Length of hospital stay (days), *median (IQR)* ^c^				
Minor adverse events				
Bradycardia, not requiring treatment,* n (%)*				
Hypotension, not requiring treatment,* n (%)*				
Main stem bronchial intubation,* n (%)*				
Oesophageal intubation with immediate recognition,* n (%)*				
Emesis without aspiration,* n (%)*				
Epistaxis,* n (%)*				
Dental or lip trauma,* n (%)*				
Major adverse events				
Cardiac arrest with or without return of spontaneous circulation,* n (%)*				
Oesophageal intubation with delayed recognition (> 60 s),* n (%)*				
Emesis with aspiration,* n (%)*				
Hypotension requiring treatment,* n (%)*				
Bradycardia requiring treatment,* n (%)*				
Laryngospasm,* n (%)*				
Malignant hyperthermia,* n (%)*				
Pneumothorax or pneumomediastinum,* n (%)*				
Death during current hospital admission, *n (%)* ^c^				

*SD* standard deviation, *IQR* interquartile range, *CI* confidence interval

^a^Adjusted for study site only

^b^Adjusted for age at randomisation, operator level and study site

^c^Limited to those patients with one enrolment per admission or multiple enrolments receiving the same randomised treatment

^d^Patients with an ICU admission only

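### Two different rules define who is analysed for death, ventilator-free days and length of stay, and both exclude children on enrolment count, which is known only after the first randomisation

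*SAP article*

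**What the plan says.** The Statistical principles section sets intention to treat as the basis of the primary analysis: "each randomised intubation encounter will be analysed based on the allocated treatment group, independent of compliance with the treatment delivered". It then allows repeat participation: "If patients are required to be intubated more than once, they can be re-enrolled and re-randomised". It notes that a child may therefore receive different study interventions within one admission.

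For the admission-level secondary outcomes (ventilator-free days, ICU stay, hospital stay and death) the same section restricts the population: "only those patients with one enrolment per admission will be included in the primary and per-protocol analyses".

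Table 4, under Adverse events and protocol deviations, attaches footnote c to the same four outcomes. The footnote reads: "Limited to those patients with one enrolment per admission or multiple enrolments receiving the same randomised treatment".

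Under Outcome definitions, ventilation-free days are "defined as the duration of respiratory support for all episodes with an ETT in situ for the first 28 days after randomisation", with a score of 0 for death within 28 days. ICU and hospital stay run from successful intubation. Death means death in the current hospital admission.

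**The concern.** There are two problems.

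**The rules conflict.** A child enrolled twice in one admission and allocated to the same arm both times is out under the text and in under the footnote. Nothing in the SAP says which rule governs. An analyst could follow either and claim adherence, and the two results for death could differ.

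**Both rules select after randomisation.** When the first envelope is opened, nobody knows whether the child will be enrolled again. A child leaves the analysis because of something that happened later in the admission. If that later event is related to prognosis, the retained children are not the randomised population. If it is also related to the allocated arm, the two retained groups are no longer comparable. Adopting the footnote everywhere would end the conflict but not the selection.

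Mortality is where this matters most. Death has one comparative row in the plan, and that row carries footnote c. An excluded child who dies is also lost from ventilator-free days, where the SAP treats death as a competing risk.

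**Working it through.** The SAP gives no figure on this point. Its sample sizes reproduce (two-sided 0.025, 90% power, pooled variance: 2 × 408 = 816 and 2 × 129 = 258; 816 / 0.85 = 960), but the point does not depend on them.

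**1. The two rules side by side**

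| Enrolments in the admission | Statistical principles | Table 4, footnote c |
|---|---|---|
| One | kept | kept |
| Two or more, all to the same arm | dropped | kept |
| Two or more, to different arms | dropped | dropped |

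**2. How many admissions fall in the row that differs**

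The Randomisation section gives a 1:1 ratio. Treating allocations as independent, the chance that k allocations all match is 2 × 0.5^k: 50% for two enrolments, 25% for three, 12.5% for four. With blocks of 10, two envelopes from the same block match with chance 4/9 = 44%, so about half is a fair summary for two.

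**3. Share of deaths dropped by the text rule**

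The SAP gives neither a re-enrolment rate (r) nor mortality in re-enrolled (m2) and single-enrolment children (m1). All three are assumptions here.

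Share dropped = r·m2 / [r·m2 + (1 − r)·m1]

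With m2 = 15% and m1 = 4%:
- r = 5%: 0.0075 / (0.0075 + 0.0380) = 16.5%
- r = 8%: 0.0120 / (0.0120 + 0.0368) = 24.6%
- r = 12%: 0.0180 / (0.0180 + 0.0352) = 33.8%

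With m1 = 5% instead:
- r = 5%, m2 = 15%: 0.0075 / 0.0550 = 13.6%
- r = 10%, m2 = 25%: 0.0250 / 0.0700 = 35.7%
- m2 = m1 (no excess risk): the share dropped is simply r.

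**4. When the comparison between arms is biased**

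Assume the arm has no effect on death. Let r0 and r1 be the re-enrolment rates under standard care and THRIVE, with r0 at least r1, and suppose the extra children re-enrolled only under standard care also carry risk m2. After exclusion:
- standard care risk = m1
- THRIVE risk = [m1(1 − r0) + m2(r0 − r1)] / (1 − r1)

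With m1 = 5% (true risk ratio 1.00 throughout):

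| r0 vs r1 | m2 | THRIVE risk analysed | Apparent risk ratio |
|---|---|---|---|
| 5% vs 5%, or 10% vs 10% | 15% or 25% | 5.00% | 1.00 |
| 10% vs 5% | 15% | 0.0525 / 0.95 = 5.53% | 1.11 |
| 10% vs 5% | 25% | 0.0575 / 0.95 = 6.05% | 1.21 |
| 15% vs 5% | 15% | 0.0575 / 0.95 = 6.05% | 1.21 |
| 15% vs 5% | 25% | 0.0675 / 0.95 = 7.11% | 1.42 |
| any of these | 5% | 5.00% | 1.00 |

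Bias between arms therefore needs both conditions: re-enrolment differs by arm, and re-enrolled children differ in risk. Deaths are lost under either condition or neither. Analysing each admission by its first allocation excludes no one and returns 1.00 in every row.

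**The case against.** The rule has an evident reason. If a child receives both interventions in one admission, an outcome such as death in that admission has no single arm. The restriction is pre-specified and covers four secondary outcomes. No p-values are planned for binary secondary outcomes, and Table 4 has no p-value column. All of this stands, and it limits the weight of the point. It does not settle which of the two rules applies. Nor does it require exclusion, since the first allocation gives every admission one arm.

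A reader might infer more than the SAP supports:

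- **That all re-intubated children are dropped.** The restriction is on re-enrolment in the same admission. A child re-intubated without re-enrolment stays in, as does one enrolled again in a later admission.
- **That the sickest children are removed.** This is plausible, since failed extubation is a listed indication for intubation in Table 2. But a required procedure or intervention is listed too, so a second enrolment need not mean deterioration.
- **That safety oversight loses these deaths.** Cardiac arrest and the other major adverse events in Table 4 carry no footnote c. Adverse events are verified for every enrolled patient, an adverse-event list is planned for the appendix, and the DSMB reviewed data at both interim analyses. What is lost is narrower: deaths in the between-arm comparison.
- **That the mortality result is necessarily biased.** The working shows it is not when re-enrolment is unrelated to arm or to risk.
- **That the primary outcomes are affected.** In this sentence of Statistical principles, the word primary refers to the main analysis of the admission-level outcomes. Both primary outcomes use the intubation encounter as the unit and keep repeat encounters.

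**Conclusion.** The point holds in two parts. The SAP gives two incompatible populations for the same four outcomes, differing on about half of twice-enrolled admissions. Both populations are selected on information that arises after the first randomisation, against the SAP's own intention-to-treat principle.

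The consequence that follows directly from the text is that re-enrolled children (all of them, or those with mixed allocations) and any deaths among them are absent from the only planned between-arm mortality comparison. The size cannot be determined from the SAP. The figures of about 17% to 34% of deaths dropped rest on assumed re-enrolment of 5% to 12% and assumed mortality of 15% against 4%, under the text rule. Bias between arms is a conditional risk and not an established fact.

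This should be fixed, but it does not threaten the primary outcomes.

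**What to change.** State one rule, in the same words, in Statistical principles and in footnote c. Each admission contributes once, all randomised children are included, and they are analysed by the allocation of the first randomised encounter in that admission. Keep the start points given under Outcome definitions (randomisation for ventilation-free days, successful intubation for ICU and hospital stay) and apply them to that first encounter. Keep the single-enrolment set as a labelled sensitivity analysis, and report by arm how many children and deaths it excludes.

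The cost is a change of wording and of record selection, with no new data: the SAP already has secondary-outcome data verified for every enrolled patient. The change should be made before the database is closed and declared, as the SAP requires for changes after its publication.

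The downside is some dilution, because about half of twice-enrolled children will have been allocated to the other arm at the later encounter. If re-enrolled children account for a sizeable share of the deaths, that dilution is not negligible for mortality and should be acknowledged when the result is interpreted.

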### Sample size

A conservative estimate of the primary outcome of hypoxaemia is set at 16%, following an unpublished 2016 audit of data from the Queensland Children’s Hospital, which we found was comparable to a published report [1]. Assuming a clinically relevant effect size of a 50% reduction in the proportion of desaturation events from 16 to 8%, along with a type I error of 0.025 (adjusting for two primary outcomes using Bonferroni’s correction) and power of 90%, 816 intubation encounters in total are required. Successful first-attempt intubation, the second primary outcome, assumes an absolute increase from 60 to 80%, requiring 258 intubation encounters. Allowing for 15% attrition, the total sample size that will satisfy both primary outcome measures is 960 intubation encounters. An attrition rate of 15% was selected based on the assumption that a proportion of patients enrolled will have a clinical deterioration, or other clinical events, during a high-stress procedure leading to the inability to deliver the intervention or collect the outcome data required for the study.

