#### Analysis methods

##### Primary outcome measures

The primary outcome measures will be analysed using logistic regression adjusting for the treatment group and the stratification variables (age group, operator level) as fixed effects and site and patient as random effects (allowing for the same patient to be recruited more than once into the study). A model without adjustment for age group or operator level will also be reported. Unadjusted and adjusted odds ratios (ORs), 95% confidence intervals (CIs) and *p*-values for the adjusted model will be reported (Table 2). Assumptions of the models will be tested and reported on.

**Table 2 Tab2:** Intubation characteristics of participants enrolled in the Kids THRIVE trial

Characteristic	Standard care, *N* =	THRIVE, *N* =
**Intubation location,** *n (%)*		
Emergency department		
Paediatric intensive care		
Neonatal intensive care		
Others		

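### Holm's procedure would give the two primary outcomes more power than fixed Bonferroni, under the same 0.05 family-wise bound and with no extra patients: a cheap improvement, not an error

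*SAP article*

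**What the plan says.** Under Statistical principles the SAP article sets the general rule, "Statistical tests will be two-sided applying a statistical significance level of 0.05", and then the exception, "although the primary outcomes will be analysed at a level of 0.025", by Bonferroni's correction. It describes no step in which one outcome's level passes to the other.

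The Sample size section uses the same level, "along with a type I error of 0.025 (adjusting for two primary outcomes". For hypoxaemia it assumes a "50% reduction in the proportion of desaturation events from 16 to 8" per cent, "and power of 90%, 816 intubation encounters in total are required". First-attempt success without hypoxaemia "assumes an absolute increase from 60 to 80%, requiring 258 intubation encounters". After 15% attrition, "the total sample size that will satisfy both primary outcome measures is 960 intubation encounters".

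Under Primary outcome measures the planned report is "Unadjusted and adjusted odds ratios (ORs), 95% confidence intervals (CIs") and p-values, so 95% intervals will stand beside tests at 0.025.

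Under Outcome definitions the two primary outcomes are described as strongly linked, with no figure for their correlation. Under Interim analyses both reviews, at 100 and at 300 patients, are reported as done, with arms shown to the monitoring board under pseudo-labels and no unblinding requested.

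**The concern.** Bonferroni holds each outcome at 0.025 whatever happens to the other. The plan's own figures make this costly: success needs 258 encounters and the trial provides 816, so at the assumed effect its test is almost certain to be significant. Once it is, the 0.025 assigned to it could be passed on to hypoxaemia without the family-wise error exceeding 0.05. Hypoxaemia sets the size of the trial, and its planning effect, a halving of risk, is large. If only one outcome reaches its target, the fixed rule makes it harder to confirm the other. The primary objective names both outcomes, so power to show both is a relevant quantity.

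**Working it through.** **Inputs.** From Sample size: hypoxaemia 16% v 8%; success 60% v 80%; two-sided 0.025; power 90%; attrition 15%. From Randomisation: 1:1. Assumed, because the article gives no figure: a correlation of 0 to 0.9 between the two test statistics, and the smaller effects marked below.

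**Step 1: reproduce the plan's figures.** The pooled-variance formula per arm is n = [z(1−α/2)·√(2p̄q̄) + z(power)·√(p₁q₁+p₂q₂)]² / (p₁−p₂)², with z(0.9875) = 2.2414 and z(0.90) = 1.2816.
- Hypoxaemia: (2.2414·√0.2112 + 1.2816·√0.2080)² / 0.08² = 407.3, so 408 per arm and 816 in total.
- Success: (2.2414·√0.42 + 1.2816·√0.40)² / 0.20² = 128.05, so 129 per arm and 258 in total.
- Attrition: 816 / 0.85 = 960.

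All three agree with the article.

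**Step 2: power at 408 per arm.** Power = Φ{[|p₁−p₂|·√n − z(1−α/2)·√(2p̄q̄)] / √(p₁q₁+p₂q₂)}.
- Success, 60% v 80%, at 0.025: Φ(4.09), above 99.99%.
- Hypoxaemia, 16% v 8%, at 0.025: Φ(1.285) = 90.1%.
- Hypoxaemia, 16% v 8%, at 0.05: Φ(1.568) = 94.2%.

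At the plan's effects Holm would therefore almost always test hypoxaemia at 0.05. For scale, 90% power at 0.05 needs 690 encounters, against 816 at 0.025.

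**Step 3: both rules compared.** Two simulations were used, both with 408 per arm: a bivariate-normal one (1,000,000 draws per setting, correlation 0 to 0.9), and a multinomial one (400,000 trials; each encounter a success, a hypoxaemia, or another failure; pooled z-tests). Where the two differ slightly, ranges are shown.

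| Scenario | Power for | Bonferroni | Holm |
|---|---|---|---|
| Plan's rates | hypoxaemia, and both | 90–91% | 94–95% |
| Success 60 v 70% (assumed), hypoxaemia 16 v 8% | success | 78% | 84% |
| Same | both | 70–77%, multinomial 73.5% | 80–84%, multinomial 82% |
| Hypoxaemia 16 v 10% (assumed), success 60 v 80% | hypoxaemia | 62% | 72–73% |
| Hypoxaemia 16 v 10%, success 60 v 66% (assumed) | hypoxaemia | 62% | 64–65% |
| Same | both | 27% | 36% |

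Power to show at least one outcome is identical under the two rules in every scenario, because both start by comparing the smaller p-value with 0.025. If all 960 encounters are evaluable, hypoxaemia power at the plan's rates goes from 94.3% to 96.9% by the Step 2 formula.

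**Step 4: error rates.**
- Both nulls true: the family-wise error is the same for both rules, 0.036 to 0.050 over correlations 0.9 to 0, and about 0.045 in the multinomial model.
- Hypoxaemia null true, success truly 60 v 80%: hypoxaemia is falsely declared in 2.5% of trials under Bonferroni and 5.0% under Holm.

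The 0.05 bound holds throughout, but when only one null is true Holm uses it in full.

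**The case against.** The strongest reply is that nothing here is wrong. Sample size and Statistical principles agree on 0.025, the figures reproduce, and the 90% target is met. That stands, and it limits the point to an improvement. Three stronger readings might tempt a reader, and the documents do not support them.

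*That Bonferroni leaves the trial short of power.* It does not: power at the plan's rates is 90.1%.

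*That Holm is free because the family-wise error is the same.* Only the 0.05 bound is the same. When success truly improves, the false-positive rate for hypoxaemia doubles, from 0.025 to 0.05.

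*That Holm rescues hypoxaemia by ten points.* This needs hypoxaemia to miss its target while success still gains its full 20 points. Success is defined as a first attempt without hypoxaemia and the article calls the outcomes strongly linked, so that combination cannot be taken for granted. With success at 66% the gain on hypoxaemia is about two points, and the larger gain is in showing both.

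Two practical objections also stand in part. A second-step rejection has no simple matching simultaneous interval: with p = 0.04 at that step, the result is significant while a 97.5% interval includes 1. Under the present rule, 97.5% intervals would match the tests exactly. The planned 95% intervals do not match 0.025 tests either, so the level needs stating under both rules, but this mismatch is not an argument for Holm.

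The change would also come after an efficacy review at 300 patients. The pseudo-labelled arms and the absence of unblinding make it defensible if it is declared in time, but it relaxes a published criterion and must be seen to be made without knowledge of the results.

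**Conclusion.** The point holds as a cheap, optional gain in efficiency. Holm dominates Bonferroni under the same 0.05 family-wise bound and at the same sample size. At the plan's rates with 816 evaluable encounters the gain is about 4 percentage points, for hypoxaemia and for showing both outcomes. It is about 9 points for showing both if success rises only to 70%, and nil for showing at least one.

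The family-wise bound holds under any dependence. The sizes rest on two-sample tests of independent encounters, not on the planned mixed logistic models with site and patient effects, and on assumed correlations and smaller effects. The gains under the planned models may differ somewhat; the ordering of the two rules will not.

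**What to change.** In Statistical principles, replace the fixed 0.025 rule for the primary outcomes with Holm: compare the smaller of the two primary p-values with 0.025; only if it is significant, compare the other with 0.05. Apply it to the p-values from the adjusted models, which are those the plan reports.

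Keep 0.025 as the planning level in Sample size; 816, 258 and 960 stay as they are.

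In Primary outcome measures, say that the decision follows the Holm p-values and name the level of the reported intervals. If 97.5% is chosen, add that an interval may include 1 beside a second-step rejection.

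Fix and declare the change before treatment labels are unmasked, and record that both interim reviews had already taken place. The SAP already commits to declaring changes made after publication.

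The cost is a few sentences and a declared amendment, no patients and no data. The statistical price is the error rate of up to 0.05 for one outcome when the other truly improves, and the loss of a simple matching interval at the second step. If the investigators prefer the stricter rule, keeping Bonferroni with 97.5% intervals is also coherent.
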